### Outcome measures

The primary end point is the incidence of chest wall tract metastasis 6 months from randomisation. If a patient raises suspicion that a chest wall nodule had developed at telephone follow-up, they will be invited to attend an outpatient appointment with the investigator. If there is clinical evidence of a chest wall metastases, a chest wall metastasis cardio respiratory fitness (CRF) is completed using the clinic date as date of chest wall metastasis.

The secondary end points are:
Time from randomisation to chest wall tract metastasis (recorded on chest wall metastasis CRF)Position of chest wall tract metastasis recurrence in relation to radiotherapy field in patients randomised to experimental arm (in field/out-of-field, recorded on chest wall metastasis CRF)Acute and late skin radiotherapy toxicity (recorded by CTCAE v4.0 at baseline and at each outpatient visit on CRF)Pain from chest wall tract metastasis (recorded by VAS pain scores recorded on chest wall metastasis CRF)

### Sample size calculation

The crude rate of tract metastases following chest wall intervention until death, based on historical data, is expected to be 15%. It is estimated that the majority of events will occur within 6 months of the intervention. A reduction in the incidence of chest wall nodules from 15% to 5% in favour of radiotherapy would be clinically significant. Based on a two-arm trial with a 5% significance level, two-sided test and 80% power this would require 280 patients. Furthermore it is anticipated that 25% of patients will not survive for 6 months therefore an additional 94 patients will be required, making the total number of patients to be enrolled 374.

### Analysis

#### Incidence of chest wall tract metastasis

All patients randomised will be analysed on an intention-to-treat basis. A two-sided χ^2^ test of proportions of chest wall tract metastasis at 6 months between the control and experimental arms will be used with a 5% significance level. Secondary analysis using logistic regression will be used to investigate treatment after adjusting for significant baseline prognostic variables.

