## Introduction

Malignant pleural mesothelioma (MPM) is almost exclusively linked to asbestos exposure with a latency period that is usually more than 30 years and prognosis is poor.^1–4^ The median survival in the UK is 8.8 months and the 1-year survival 38.5%.^5^

Diagnosis of mesothelioma is usually made by pleural biopsy either via CT-guided needle biopsy, thoracoscopy, video-assisted thoracic surgery (VATs) or thoracotomy. Patients often have associated pleural effusions and require chest drains to relieve symptoms such as chest pain and difficulty breathing. These invasive procedures encourage tumour cell seeding at the site of the intervention, which can result in formation of a subcutaneous tumour. The rate of chest wall metastases ranges from 2% to 50%, and depends on the procedure performed.^4^
^6–14^

In an effort to minimise tumour seeding and prevent nodule development, it has been widespread practice for more than 20 years in the UK to irradiate intervention sites postprocedure—a practice known as prophylactic irradiation of tracts (PIT).

Only three randomised controlled trials, the largest with 61 patients, have assessed the role of PIT with conflicting results reported.^14–19^ One study reported a statistically significant reduction in the frequency of malignant seeding of tracts in the PIT arm compared to the control arm^14^; the other two studies did not.^15^
^16^ Systematic reviews of the literature have concluded that the randomised trials conducted to date were considered the best available evidence for PIT, but that there was insufficient evidence to definitively recommend PIT.^17–20^ Inconsistencies are also evident in current national recommendations on the use of PIT. The British Thoracic Society^21^ recommends the use of PIT to prevent chest wall nodule formation following an interventional procedure. In contrast, the Cancer Care Ontario Programme^22^ stated that a recommendation for PIT in MPM could not be made due to inconsistent evidence, reflecting a lack of high-quality data. Similarly, in 2010 the European Respiratory Society stated “The value of prophylactic radiotherapy is questionable”^23^ and the European Society of Medical Oncology (ESMO) clinical recommendations for diagnosis, treatment and follow-up of MPM state that “it remains impossible to draw definitive conclusions regarding its efficacy”.^24^

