### Randomisation procedure

Patients will be randomised by phone or fax on a 1:1 basis to one of two treatment arms. A variant of an adaptive biased coin randomisation method will be used to favour balance between treatment arms in the four strata formed from the following two factors:
Histology (epithelioid or not epithelioid)Intention to give chemotherapy

Randomisation will be undertaken centrally by Manchester Academic Health Science Centre Clinical Trials Unit (MAHSC-CTU).

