#### Time to chest wall tract metastasis

Kaplan-Meier curves will be drawn for each treatment group. Time to chest wall tract metastasis will be compared using a two-sided log rank test with a 5% level of significance. Cox-proportional hazards models will be used to investigate the effect of treatment after adjusting for stratification factors and other significant baseline variables.

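### The primary chi-square test and the log-rank test ignore the randomisation strata, and the secondary logistic model, unlike the Cox model, does not guarantee them

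*Protocol article*

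**What the plan says.** Under Randomisation procedure the protocol article states: "A variant of an adaptive biased coin randomisation method will be used to favour balance between treatment arms in the four strata". The two factors are histology (epithelioid or not) and the intention to give chemotherapy.

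Under Incidence of chest wall tract metastasis the primary analysis is: "A two-sided χ^2^ test of proportions of chest wall tract metastasis at 6 months between the control and experimental arms will be used". No stratification is mentioned. The same section then adds: "Secondary analysis using logistic regression will be used to investigate treatment after adjusting for significant baseline prognostic variables".

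Under Time to chest wall tract metastasis the comparison is an unstratified two-sided log-rank test, followed by: "Cox-proportional hazards models will be used to investigate the effect of treatment after adjusting for stratification factors and other significant baseline variables".

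The Introduction says of the event itself: "The rate of chest wall metastases ranges from 2% to 50%, and depends on the procedure performed". The inclusion criteria admit VATS, open surgical biopsy, local anaesthetic thoracoscopy and chest drain. Procedure type is neither a randomisation factor nor a named covariate.

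**The concern.** If allocation is forced towards balance on a factor that predicts outcome, the arms differ less by chance than an unstratified test assumes. That test is then somewhat conservative and gives up some precision. The usual practice is to carry the balancing factors into the analysis.

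The adjusted analyses also follow two different rules. The Cox model always contains the strata. The logistic model, which supports the primary end point, contains them only if they count as significant. Choosing covariates by significance when events are few tends to miss real predictors. It also makes the adjusted estimate depend on which variables passed, and the reported standard error ignores that step. What is at stake is a little efficiency in the main tests and the reproducibility of the secondary adjusted results.

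**Working it through.** **1. The plan's own figure.** Inputs from Sample size calculation: 15% v 5%, two-sided 5%, 80% power, 25% dead by 6 months. With pooled variance and no continuity correction:

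n per arm = [1.960·√(2·0.10·0.90) + 0.842·√(0.15·0.85 + 0.05·0.95)]² / 0.10² = (0.8315 + 0.3521)² / 0.01 ≈ 140.1.

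That is 141 when rounded up (282 in total), against the stated 280. Power at 140 per arm is 0.7997. Inflation: 280 / 0.75 = 373.3, so 374. The sample size therefore assumes the unadjusted test, and that test delivers the planned power.

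**2. Expected events.** 140 × 0.15 + 140 × 0.05 = 21 + 7 = 28.

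**3. How conservative the unstratified test can be.** Under the null, with exact balance within strata, the true variance of the difference is proportional to the weighted mean of p(1−p) within strata. The chi-square test uses p̄(1−p̄). With R as the ratio of the two, the actual size is 2[1 − Φ(1.96/√R)].

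- Assumed rates 8% and 22% in two equal strata: R = (0.5·0.0736 + 0.5·0.1716) / (0.15·0.85) = 0.1226/0.1275 = 0.962. The critical value becomes 1.999 and the size 4.6% (4.5% by simulation).
- Assumed extreme rates 2%, 5% and 40% in 35%, 35% and 30% of patients: R = 0.0955/0.1236 = 0.772. The critical value becomes 2.230 and the size 2.6% (2.6% by simulation).

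Without forced balance, simulation gave about 5% in both cases. The planned biased coin only favours balance, so these are upper limits on the conservatism.

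**4. Power.** Simulation of 280 patients, balanced within the four strata, 15% v 5%, 3,000 replicates per row. The article gives no prognostic strengths. The assumptions are 30% non-epithelioid, 50% intended for chemotherapy, 50% with a higher-risk procedure, and one odds ratio (OR) applied to each of the three factors. CMH is the Cochran-Mantel-Haenszel test on the four strata. The selected model keeps covariates with univariable p < 0.05 out of seven candidates, four of them noise. Entries are percentages.

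| OR | Chi-square | CMH | Logistic, strata | Logistic, strata + procedure | Logistic, selected | Chi-square type I error (15% v 15%) |
|---|---|---|---|---|---|---|
| 1.0 | 81.4 | 81.5 | 82.4 | 82.3 | 81.7 | 5.2 |
| 1.5 | 82.7 | 83.0 | 84.0 | 84.4 | 83.6 | 5.2 |
| 2 | 81.6 | 82.3 | 82.9 | 83.2 | 82.9 | 4.8 |
| 3 | 82.2 | 83.4 | 84.4 | 85.2 | 84.5 | 4.5 |

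CMH gains 0.1, 0.3, 0.7 and 1.2 points. A second run (2,500 replicates, OR 1.5, 2 and 3) gave 0.2, 0.6 and 1.4. Logistic regression with strata and procedure gains 0.9 to 3.0 points (3.6 in the second run at OR 3), but part of that reflects a slightly liberal likelihood-ratio test (type I error 5.3% to 5.9%). The Monte Carlo standard error of one power figure is √(0.82·0.18/3000) = 0.7 points, and of one type I figure √(0.05·0.95/3000) = 0.4 points. The 4.5% is thus compatible with 5%, though its direction agrees with step 3.

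**5. What screening does.** At OR 1.5, 2 and 3 (second run):

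- both strata were retained in 2%, 13% and 47% of trials;
- procedure was retained in 16%, 35% and 69%;
- the selected model and the model with strata fixed disagreed on significance in 1.5%, 1.8% and 2.4%.

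**The case against.** The strongest reply is that an unadjusted primary test supported by adjusted secondary models is a common and valid design, and that the trial was sized for exactly that test. This stands. No error in the primary result follows from ignoring the strata, only a little forgone efficiency.

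Three stronger readings are tempting, and the article supports none of them.

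- *The logistic model leaves out the strata and procedure type.* It does not exclude them; either may enter if judged significant. The fault is that they are not guaranteed.
- *The Introduction's 2% to 50% range shows a large loss from not using procedure type.* The Introduction's list of procedures includes CT-guided needle biopsy, which is not among the eligible interventions, and thoracotomy, which is excluded. The spread among eligible procedures is not given. A simulation with rates of 2%, 5% and 40% shows power rising from 81.8% to 86.0% on stratification. That pattern resembles procedure type, however, and a test stratified by histology and chemotherapy intent would not recover it.
- *The primary p-value depends on covariate selection.* Selection enters only the logistic and Cox models.

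It can also be said that significant may mean important, since the article speaks elsewhere of clinical significance, and that a candidate list and threshold normally belong in an analysis plan that is not shown. Their absence is indeed no finding. Even on that softer reading, though, the logistic wording does not secure the strata that the Cox wording names. That difference lies in the stated text.

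**Conclusion.** The point holds as a modest matter of precision and specification, not of validity. The chi-square test keeps its planned 80% power. Ignoring the strata makes it at most slightly conservative and costs about 0 to 1 percentage point of power against a Cochran-Mantel-Haenszel test (1.4 at most in either run). This assumes odds ratios up to 3 for each factor and near-exact balance within strata. The true prognostic strength is not given, and the loss would be larger only if the strata were much stronger predictors than that.

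The clearer defect is the mismatch between the two adjusted models. If the logistic wording is applied as a 5% screen, at least one randomisation factor would be dropped in more than half of the simulated trials even at an odds ratio of 3. The effect on conclusions is small: about 2% of trials change significance status, and power is nearly the same. The reported secondary estimate would nevertheless rest on a data-driven covariate set.

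**What to change.** - Make the primary comparison a Cochran-Mantel-Haenszel test over the four randomisation strata, and stratify the log-rank test in the same way. The plain chi-square result can be reported alongside.
- Name histology and chemotherapy intent as fixed covariates in the logistic model, as is already done for the Cox model.
- Prespecify procedure type in both models as a coarse covariate, for example with two levels, because the Introduction says the nodule rate depends on it.
- Delete selection by significance from both models.

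The cost is a small protocol wording change, more than an analysis-plan edit because the primary test is named in the protocol. It should be made and dated before the analysis. No new data should be needed, since procedure type has to be known to establish eligibility. The covariate set must stay small: treatment, histology, chemotherapy intent and a two-level procedure variable make four coefficients, or 28/4 = 7 events each. A three-level procedure variable would leave 28/5 = 5.6.

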#### Time to chest wall tract metastasis

Kaplan-Meier curves will be drawn for each treatment group. Time to chest wall tract metastasis will be compared using a two-sided log rank test with a 5% level of significance. Cox-proportional hazards models will be used to investigate the effect of treatment after adjusting for stratification factors and other significant baseline variables.

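### Kaplan-Meier curves for time to chest wall nodule, with death outside the event and no competing-risk method named, would overstate the nodule incidence patients experience in both arms

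*Protocol article*

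**What the plan says.** The protocol article, under Outcome measures, lists as a secondary end point "Time from randomisation to chest wall tract metastasis (recorded on chest wall metastasis CRF"). Death is not part of that event.

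Under Time to chest wall tract metastasis it fixes the methods: "Kaplan-Meier curves will be drawn for each treatment group", and "Time to chest wall tract metastasis will be compared using a two-sided log rank test with a 5% level of significance". Cox models adjusted for stratification factors and other baseline variables follow. The section names no competing-risk or cumulative incidence method and does not say how deaths without a nodule are handled.

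The article gives these figures for mortality and nodule incidence:
- Introduction: "The median survival in the UK is 8.8 months and the 1-year survival 38.5"%.
- Sample size calculation: "it is anticipated that 25% of patients will not survive for 6 months".
- Sample size calculation: "The crude rate of tract metastases following chest wall intervention until death, based on historical data, is expected to be 15"%, and "It is estimated that the majority of events will occur within 6 months of the intervention".
- Sample size calculation: "A reduction in the incidence of chest wall nodules from 15% to 5% in favour of radiotherapy would be clinically significant".
- Trial design: follow-up lasts up to 2 years after randomisation.

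**The concern.** A patient who dies without a nodule can no longer develop one. Censoring that patient in a Kaplan-Meier analysis treats them as still at risk and redistributes their chance of a nodule among the survivors. One minus Kaplan-Meier (1-KM) then answers what the nodule risk would be if death were abolished. The trial's question is framed in what happens to real patients: the 15% planning rate is a crude rate with death as the end of risk, and the target is an absolute fall to 5%.

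Both mortality figures in the article imply that most patients die within the 2-year follow-up. A clinician who reads nodule rates, or the absolute benefit of PIT, off the later part of such curves would read values that are too high in both arms, and so a difference that is too large.

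**Working it through.** **The plan's own figures first.** For 15% against 5%, two-sided 5% and 80% power, the pooled-variance formula without continuity correction gives 141 per arm, or 282. At 140 per arm the power is 79.97%, so 280 reproduces. Then 280 / 0.75 = 373.3, rounded up to 374. The plan states no figure for the time-to-nodule curves, so the size of the effect needs a model.

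**Death hazard m, per month, two versions.**
- Trial planning figure, 25% dead at 6 months: m = -ln(0.75)/6 = 0.04795. Survival at 24 months = exp(-24m) = 31.6%.
- General UK median of 8.8 months: m = ln(2)/8.8 = 0.07877. Survival at 12 months = 38.9%, close to the quoted 38.5%; at 24 months it is 15.1%.

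**Nodule hazard.** Take 15% as the crude incidence until death. Let s be the share of those events occurring by 6 months. The article says only that it is a majority, so s is an assumption, varied from 55% to 90%. The hazard is l1 up to 6 months and l2 afterwards, with time counted from randomisation.
- l1 solves l1/(l1+m) × (1 - exp(-6(l1+m))) = 0.15s.
- Alive and nodule-free at 6 months: S6 = exp(-6(l1+m)).
- l2 = m × q/(1-q), where q = 0.15(1-s)/S6.

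**Quantities compared at 24 months.**
- True cumulative incidence = 0.15s + S6 × l2/(l2+m) × (1 - exp(-18(l2+m))).
- 1-KM with deaths censored = 1 - exp(-6·l1 - 18·l2).

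**One case written out** (25% dead at 6 months, s = 70%). l1 = 0.02139; S6 = 0.6597; q = 0.045/0.6597 = 0.0682; l2 = 0.00351.
- At 6 months: true 10.5%; 1-KM = 1 - exp(-0.1283) = 12.0%; ratio 1.15.
- At 24 months: true = 0.105 + 0.0450 × 0.604 = 13.2%; 1-KM = 1 - exp(-0.1283 - 0.0632) = 17.4%; ratio 1.32.

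**Range, control arm** (ratios from unrounded values):

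| Death rate | Share s by 6 months | 6-month ratio | 24 months: true | 24 months: 1-KM | 24-month ratio |
|---|---|---|---|---|---|
| 25% dead at 6 months | 90% | 1.15 | 14.38% | 17.22% | 1.20 |
| 25% dead at 6 months | 70% | 1.15 | 13.22% | 17.43% | 1.32 |
| 25% dead at 6 months | 55% | 1.15 | 12.41% | 17.70% | 1.43 |
| 8.8-month median | 90% | 1.25 | 14.65% | 20.26% | 1.38 |
| 8.8-month median | 70% | 1.25 | 14.04% | 23.58% | 1.68 |
| 8.8-month median | 55% | 1.25 | 13.65% | 26.17% | 1.92 |

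**Absolute difference between arms.** Repeat the calculation with 5% until death in the PIT arm and s = 70%. At 24 months with 25% dead at 6 months, the true difference is 13.22 - 4.38 = 8.8 points and the 1-KM difference is 17.43 - 5.77 = 11.7 points. With the 8.8-month median they are 14.04 - 4.65 = 9.4 and 23.58 - 7.82 = 15.8 points.

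**Other reading of the 15%.** The abstract attaches 15% and 5% to 6 months after randomisation. Set as true 6-month incidence, they give 6-month ratios of 1.15 (25% dead) and 1.24 to 1.25 (8.8-month median). If the nodule hazard then falls to one quarter after 6 months, the 24-month ratios across both arms are 1.37 to 1.39 and 1.60 to 1.65. The direction is the same in every case.

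**The case against.** The strongest reply is that censoring at death is nowhere written. The article condenses a fuller protocol, an analysis plan may exist, and either could specify how deaths are treated or add a competing-risk display. This stands as a limit on certainty: the point is conditional on ordinary use of the named method. It does not remove the point, because the article names a specific estimator for an event that excludes death, and ordinary use of that estimator censors nodule-free deaths.

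The second reply is that little depends on the curve. This also stands in part. The end point is secondary, and the article does not commit to quoting rates or absolute reductions from the curves. The milder 25% mortality figure is the trial's own and belongs to the selected performance status 0-2 population, so it should lead. On that figure the 6-month gap is only about 1.5 points (12.0% against 10.5%, s = 70%).

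A reader might infer more than the documents support:
- That the log-rank test and Cox model are invalid. They are not; with deaths censored they compare cause-specific hazards.
- That the curve must contradict the primary 6-month proportion in a known direction. That depends on how early deaths enter the denominator. The analysis section includes all randomised patients, while the sample size adds patients to cover early deaths. With s = 70% and 25% dead, dropping nodule-free early deaths would give 0.105/(0.105 + 0.660) = 13.7%, above the 12.0% from 1-KM.
- That dates of death are already collected. The article does not say so.

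**Conclusion.** The point holds as an improvement to a secondary, descriptive analysis. If nodule-free deaths are censored, 1-KM overstates experienced nodule incidence in both arms. The direction does not depend on the modelling.

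The size does. With 15% crude incidence until death and the trial's own mortality figure, the ratio is about 1.15 at 6 months and 1.20 to 1.43 at 24 months. With the general UK median survival it is about 1.25 and 1.38 to 1.92. These rest on piecewise-constant hazards and an assumed early share of 55% to 90%. No single ratio should be quoted as the bias.

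It would be tempting to conclude that the trial's main result is at risk. The documents do not support that: the primary chi-square test of 6-month proportions and the 280/374 sample size make no use of Kaplan-Meier.

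**What to change.** - Present Aalen-Johansen cumulative incidence curves by arm as the display of absolute nodule risk, with death without nodule as the competing event.
- Report the 6-, 12- and 24-month estimates with confidence intervals.
- Show the cumulative incidence of death without nodule beside them.
- Keep the log-rank test and Cox model, labelled as cause-specific hazard analyses.

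A Kaplan-Meier plot could stay as a companion to those two analyses, provided it is not offered as incidence.

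The cost is a change of wording and a little more analysis with standard software. The date of death must be available for each patient. The article does not state that it is recorded, but any censoring at death would need it too, so this should be confirmed.

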#### Toxicity

Skin toxicity will be assessed according to NCI Common Terminology Criteria for Adverse Events V.4.0. The proportions of patients experiencing a grade of 3 or above acute toxicity, including acute radiation morbidity, or late radiation morbidity will be compared between the treatment groups using a two-sided χ^2^ test with a 5% level of significance. Acute toxicity will be defined as toxicities occurring from start of treatment to 3 months after completion; late toxicity will be defined as toxicities occurring between 3 months and 2 years after completion of treatment.

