Currently in the UK the routine use of PIT in patients with MPM depends on locality. A 2008 UK survey showed that 75% of radiotherapy centres are routinely using PIT.^17^ In addition, the small number of patients recruited to each arm, the high death rates, and overestimation of the rate of chest wall metastasis in the control arms, question whether the three previous randomised controlled trials were adequately powered. Furthermore, recent evidence shows that portal tracts are not always perpendicular to the skin^25^ and thus the small radiation fields centred on the chest wall scar employed by the previous negative studies may have been suboptimal.

There is now strong evidence to support the role of palliative chemotherapy in patients with MPM^26^ which is approved in the UK by the National Institute of Clinical Excellence (NICE).^27^ Importantly, the previous studies were conducted before palliative chemotherapy was widely used in MPM. Therefore, the role of PIT in the era of effective palliative chemotherapy remains undefined. In addition, no previous studies have used validated pain scoring tools to assess pain from tract metastases.

We believe a trial is essential for the following reasons: first an adequately powered RCT employing radiotherapy techniques ensuring adequate coverage of the entire portal tract will establish whether PIT should be offered routinely to patients with MPM after chest wall intervention in the era of palliative chemotherapy; second to establish whether chest wall metastases are symptomatic and thus, whether PIT, if effective, is clinically significant.

The hypothesis for this trial is that prophylactic irradiation of tracts will reduce the incidence of chest wall nodules from 15% to 5%. The primary objective of the PIT study is to determine the efficacy, as assessed by the incidence of chest wall metastasis, of prophylactic irradiation of tracts following invasive chest wall intervention in malignant pleural mesothelioma compared to no prophylactic radiotherapy. Secondary objectives include: the description of the toxicity of PIT; time from randomisation to chest wall tract metastasis in patients undergoing PIT compared with the no prophylactic radiotherapy; the assessment of pain from chest wall metastasis.

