### Trial monitoring

The trial management group (TMG) is responsible for reviewing the trial's day-to-day activities, the overall supervision of the trial and ensure that it is being conducted in accordance with the principles of good clinical practice and relevant regulations. The group should agree any protocol amendments and provide advice to the investigators on all aspects of the trial. The TMG meets twice a year and includes patient/carer representatives, respiratory physicians, thoracic surgeons, clinical oncologists, medical oncologists and clinical nurse specialists. Three additional members who are independent of the trial have been appointed and will be available to advise the TMG should any issues arise requiring an independent viewpoint.

An Independent Data Monitoring Committee (IDMC) will not be appointed for this trial as PIT is currently widely used in clinical practice, it is not a new treatment and we not envisage that any safety issues will arise.

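### The only stated between-arm comparison of acute skin toxicity is at grade 3 or above, so grades 1–2 never enter it, and the test says little if severe events are rare

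*Protocol article*

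**What the plan says.** Three parts of the protocol article bear on this.

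- **Introduction, secondary objectives.** The toxicity objective is "the description of the toxicity of PIT".
- **Outcome measures.** Acute and late skin toxicity is a secondary end point, "recorded by CTCAE v4.0 at baseline and at each outpatient visit on CRF". No minimum grade for recording is stated.
- **Analysis, Toxicity.** The quantity to be compared is "The proportions of patients experiencing a grade of 3 or above acute toxicity, including acute radiation morbidity". The same sentence then adds late morbidity, without giving it a grade of its own. The arms are compared "using a two-sided χ^2^ test with a 5% level of significance". This is the only toxicity comparison described. The section mentions no use of the baseline grade and no summary of lower grades.

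The document gives no expected rate for any grade of skin toxicity and no power for this comparison. The nearest statement is under Trial monitoring, where the reason for having no IDMC includes that "it is not a new treatment and we not envisage that any safety issues will arise".

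**The concern.** The data collected and the objective are both wider than the comparison. A graded measurement, taken at baseline and at repeated visits, is reduced for acute toxicity to yes or no at grade 3. Two patients with grades 0 and 2 count the same.

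The Radiotherapy section describes bolus to bring more than 90% of the prescribed dose to the skin surface, so skin is where the plan itself looks for toxicity. The scar is also recent: patients must be able to start radiotherapy within 42 days of the intervention, and the scar must be visible at randomisation. A grade read without its baseline may therefore mix wound effects with radiation effects, although the baseline grade is there to separate them.

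PIT is preventive, and the Introduction gives a median survival of 8.8 months. Its value depends on nodules avoided against harm caused. If the toxicity result is one non-significant test on few events, a reader may take it as reassurance that it cannot give.

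**Working it through.** **The plan's own figures.** There is none for toxicity. The primary sample size gives the arm size, so I checked that first. For 15% v 5%, two-sided 5%, 80% power, pooled variance and no continuity correction:

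n per arm = [1.960·√(2·0.10·0.90) + 0.8416·√(0.15·0.85 + 0.05·0.95)]² / 0.10² = (0.8316 + 0.3521)² / 0.01 ≈ 140.1, so 141 per arm or 282 in all.

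The plan states 280, at which power is 79.97%. Then 280/0.75 = 373.3, so 374. The figures reproduce, and 374 at 1:1 is 187 per arm.

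**Events needed for significance.** With x cases on PIT, none in control, n = 187 and N = 374, Pearson's statistic reduces to χ² = N·x/(N − x). With continuity correction it is N·(x − 1)²/[x·(N − x)].

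| PIT v control cases | χ² p | corrected χ² p | Fisher p |
|---|---|---|---|
| 3 v 0 | 0.082 | 0.246 | 0.248 |
| 4 v 0 (2.1%) | 0.044 | 0.132 | 0.123 |
| 5 v 0 | 0.024 | 0.072 | 0.061 |
| 6 v 0 (3.2%) | 0.014 | 0.040 | 0.030 |

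The article does not say whether a correction is used. That choice alone moves the threshold from 4 cases to 6.

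**Power, with the control rate assumed to be 0%.** Power is P(X ≥ 4) uncorrected and P(X ≥ 6) corrected, with X binomial (187, p). For p = 1%: 1 − (0.1527 + 0.2884 + 0.2709 + 0.1688) = 0.119.

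| Assumed PIT grade 3+ rate | Expected events | Uncorrected | Corrected |
|---|---|---|---|
| 0.5% | 0.9 | 1.5% | 0% |
| 1% | 1.9 | 12% | 1% |
| 2% | 3.7 | 52% | 17% |
| 3% | 5.6 | 82% | 49% |
| 5% | 9.4 | 98% | 91% |

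With 140 per arm (the plan's allowance for 25% deaths by 6 months, relevant mainly to late toxicity), uncorrected power is 5% at a 1% rate and 31% at 2%.

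**Approximation.** With equal arms, the expected count per arm is half the total events. At a 1% rate that is 1.87/2 ≈ 0.9, well below the usual minimum of 5.

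**What zero events would show.** The exact two-sided 95% upper limit for 0/187 is 1 − 0.025^(1/187) = 1.95%.

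**Would an ordinal test do better?** That depends on the assumed grades. Percentages are for grades 0/1/2/3, with 187 per arm, by simulation.

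| Control | PIT | Grade 3+ χ² power | Linear trend power |
|---|---|---|---|
| 95/4/1/0 | 79/15/5/1 | 12% | >99% |
| 80/15/5/0 | 79/15/5/1 | 12% | 8% |
| 80/15/5/0 | 75/17/5/3 | 81% | 39% |

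The trend test gains when the excess is in mild grades. It loses when control patients also carry mild grades and the excess is severe. Neither analysis covers both cases. These runs did not model baseline grades.

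**The case against.** The strongest case against the point has four parts.

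1. **Silence is not omission.** The article condenses protocol V.3.0, and an SAP may exist. A table of worst grade by arm is routinely left to those documents. Graded recording and an objective of description both point towards such a table. This stands: a reader might infer that lower grades are dropped altogether, but the article shows only that they are outside the stated comparison.
2. **No low rate is stated.** A reader might infer that the plan itself expects an almost empty grade 3+ cell. The sentence under Trial monitoring explains why no IDMC is appointed and gives no rate. At 3–5% on PIT against 0%, the uncorrected test is adequate. This stands too, as does the lack of any documented rate showing that grades 1–2 are the commoner harm.
3. **Grade 3+ is a legitimate cut.** It marks clinically important harm, and an ordinal test can dilute a severe excess. This stands and rules out replacing the grade 3+ comparison.
4. **The late limit is ambiguous.** The sentence can be read as applying the grade limit to acute toxicity only, with late morbidity of any grade compared. It does not support a claim that late toxicity is also confined to grade 3 or above.

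Nor does the article say that a non-significant result will be read as equivalence. What remains is that a comparison is fixed in the text, it excludes grades 1–2 for acute toxicity whatever the rates, and the chosen test is a poor one if events are few.

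**Conclusion.** The point holds in a limited form. For acute toxicity, the stated comparison is narrower than the objective and the data, and it carries no information on grades 1–2 at any event rate. Its value for severe toxicity depends on a rate the document does not give. If grade 3+ events occur in 0–1% of PIT patients and in no controls, uncorrected power is at most about 12% and the χ² approximation is poor. If they occur in 3–5%, uncorrected power is about 82–98%.

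No figure in the plan is wrong, the primary analysis is unaffected, and this is a secondary end point. It is an improvement the sponsor could make, not an error that must be corrected.

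**What to change.** In the Toxicity section:

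- Keep the grade 3+ comparison, but report it as a risk difference with an exact 95% confidence interval and an exact test in place of χ².
- State whether the grade limit applies to late morbidity.
- Add the worst CTCAE skin grade per patient in each period, counted where it is worse than the recorded baseline grade, tabulated by grade (0, 1, 2, 3+) and arm. Accompany it with an ordinal comparison (trend or Wilcoxon), labelled as supplementary to the grade 3+ line.

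One detail has to be settled for this table and for the existing test alike. The acute and late periods are dated from the start and completion of treatment, which the no-PIT arm does not have, so an equivalent reference date for controls needs to be stated.

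The cost is some wording, one more table and one more test, with no new data. The toxicity summary may look less favourable to PIT.
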